#### Therapeutic process measure

##### *-Five Facet Mindfulness Questionnaire (FFMQ)* [59]

This questionnaire assesses five factors of mindfulness through 39 items: observing (8 items), describing (8 items), acting with awareness (8 items), not judging inner experience (8 items), and not reacting to inner experience (7 items). Items are answered on a Likert-type scale ranging from 1 (“never or very rarely true”) to 5 (“very often or always true”). The FFMQ has been shown to have good internal consistency and reliability in its Spanish validation [60].

#### Treatment expectations, opinions, and completion

##### -Expectation of treatment scale (ETS) and opinion of treatment scale (OTS)

These scales are adapted from Borkovec and Nau [61]. They include 5 items, rated from 0 (“not at all”) to 10 (“very much”), that address how logical the treatment seems, to what extent it satisfies the patient, whether it could be used to treat other psychological problems, its usefulness for the patient’s specific problem, and to what extent the treatment might be aversive. The expectation scale will be applied once the treatment rationale has been explained and after M0 to measure subjective patient expectations about the treatment they are about to receive. The opinion scale is administered when the patients have completed the treatment to assess their satisfaction with it.

In the case of the MBI groups, a question will be introduced related to the opinion about each individual module (e.g. “To what extent has this module been useful to you?“), using a visual analogue scale ranging from 0 (“nothing”) to 10 (“very much”), as well as two questions related to reviewing the materials (“Have you reviewed the last module seen in the session and all the materials it includes?”) and homework completion (“Have you done the tasks to train at home?”), with two possible responses (yes vs. no). In addition, a module completion register will be filled out.

### Data analysis

The results will be reported following CONSORT recommendations [62, 63]. Socio-demographic and clinical information will be described at baseline by means of frequencies and percentages (e.g. categorical variables) or means and standard deviations (e.g. continuous variables), and treatment conditions will be compared to ensure the success of the randomization, using the chi-square or Fisher tests and one-way ANOVA.

### Main analysis

The efficacy of the “face-to-face MBI + TAU” group compared to the “TAU alone” group will be estimated based on the main BDI-II outcome, which will be considered a continuous variable. Multilevel mixed-effects models will be developed by means of a RM design on an intention-to-treat (ITT) basis, using the restricted maximum likelihood (REML) method, in order to produce unbiased estimates of variance/covariance parameters [54]. Non-standardized slopes and 95% confidence intervals (95% CI) will be calculated by adjusting those variables that show significant differences between groups at baseline. In order to study the specific trajectories of each group throughout the trial and determine whether possible differences between groups are consistent over time, the ‘group x time’ interactions will be calculated. Cohen’s d effect sizes will be calculated at each time point using the combined standard deviation at baseline [64]. Effect sizes are small when d ≤ 0.2; medium when d = 0.5; and large when d ≥ 0.8 [65].

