**Methods:**

A randomized controlled clinical trial will be conducted in PC, with about 120 depressed patients allocated (1:1:1) to three groups: “face-to-face MBI + TAU”, “Internet-delivered MBI + TAU”, and “TAU alone”. The MBI programs will be composed of four modules. The primary outcome will be depressive symptoms, measured through the Beck Depression Inventory, assessed at pre- and post-treatment and 6- and 12-month follow-ups. Other outcomes will be mindfulness, happiness, affectivity, quality of life, and the use of healthcare services. Intention-to-treat analysis using linear mixed models adjusted for baseline scores and routine sociodemographic analysis that could show baseline differences will be conducted. Per-protocol secondary outcome analyses will also be performed.

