### Randomization and blinding

Participants who meet the inclusion criteria for the study will receive a code from the screening assessors in order to maintain participants’ confidentiality. An independent researcher unaware of the study characteristics will perform the randomization process. In order to randomly allocate the participants to one of the three conditions referred to above (face-to-face MBI + TAU, Internet delivered MBI + TAU, and TAU alone), a computer-generated random number sequence (https://www.randomizer.org/) will be used by means of a simple allocation strategy and a 1:1:1 rate. After informing the patients of the study characteristics, they will accept to participate before the random allocation and without knowing the condition to which they will be allocated. The researcher who administers baseline assessments will be blind to the patients’ treatment group. This researcher will be different from the one – also blinded – who administers the other measures throughout the study. Patients in the Internet-delivered MBI arm will complete all the measures online. GPs will be blind, but the face-to-face MBI therapist will not. Participants will not be blind to the treatment condition for ethical and practical reasons.

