### Level of significance

An alpha level of 0.05 will be established using a two-tailed test. The probability values relative to the main analysis will be adjusted according to Benjamini-Hochberg’s correction for multiple comparisons, but the secondary and exploratory analyses will not be corrected.

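### Main-model covariates are chosen by baseline significance tests, and the main analysis does not say how baseline BDI-II enters the model

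*Protocol article*

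**What the plan says.** The protocol article touches on adjustment in three places.

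- **Data analysis:** baseline characteristics are described by arm, and "treatment conditions will be compared to ensure the success of the randomization, using the chi-square or Fisher tests and one-way ANOVA".
- **Main analysis:** "Multilevel mixed-effects models will be developed by means of a RM design on an intention-to-treat (ITT) basis", with group-by-time interactions. The slopes and confidence intervals "will be calculated by adjusting those variables that show significant differences between groups at baseline". No covariate is named, and baseline BDI-II is not mentioned as one.
- **Abstract, Methods:** the analysis uses "linear mixed models adjusted for baseline scores and routine sociodemographic analysis that could show baseline differences". Here baseline scores are in the model, and the condition about differences attaches to the sociodemographic variables.

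Allocation is "by means of a simple allocation strategy and a 1:1:1 rate", with no stratification stated. On the test level, "An alpha level of 0.05 will be established using a two-tailed test". The Secondary analysis section applies the same analytical strategy to the other outcomes and comparisons.

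**The concern.** After proper randomisation, every baseline difference is a chance difference. A significance test therefore cannot show that randomisation succeeded, and it is a poor guide to what to adjust for. A covariate earns its place by predicting the outcome. A strong predictor that narrowly misses p<0.05 is left out, while a variable unrelated to BDI-II that happens to cross the line is put in. The primary model is then known only after the arms have been compared at baseline.

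The most important predictor is likely to be baseline BDI-II itself, and here the article is unclear. The abstract has it in the model. The Main analysis section makes the only adjustment it mentions conditional on significance. It does not say whether baseline BDI-II is a covariate, the first of the four outcome measurements, or neither. These choices give different estimates and different precision for the primary comparison.

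**Working it through.** **Inputs** (Sample size section): SD 5; face-to-face versus TAU difference 3.5 points at post-test; correlation r = 0.6 between baseline and post-test; 33 evaluable per arm; two-sided alpha 0.05.

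**Reproducing the plan's figure.** A two-sample comparison of 3.5 points with SD 5 needs 33 per arm for 80% power (noncentral t: 80.0%). The three-arm, four-time group-by-time test with Greenhouse-Geisser correction and the stated means gives 80.7% to 82.3% at 33 per arm, depending on visit spacing. Both agree with the stated 33.

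**How often chance picks a covariate.** Each variable passes the screen with probability 0.05. For k independent variables, the chance that at least one passes is 1 − 0.95^k. The article lists six sociodemographic variables, so 1 − 0.95^6 = 0.26. With ten variables it is 0.40 and with fifteen 0.54; these larger counts, and independence, are assumptions. The figures show how far the model depends on chance. They do not measure bias.

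**Power at post-test by use of baseline** (33 per arm; SE = SD × √(2/33); noncentral t):

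| Use of baseline BDI-II | SD of the compared quantity | SE | Power for 3.5 points |
|---|---|---|---|
| Not used | 5 | 1.23 | 80% |
| Change only (unconstrained group-by-time contrast) | 5 × √(2(1 − 0.6)) = 4.47 | 1.10 | 88% |
| Covariate (ANCOVA) | 5 × √(1 − 0.6²) = 4.00 | 0.98 | 94% |

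The ordering does not depend on the exact correlation. At r = 0.5 the change and ANCOVA powers are 80% and 90%; at r = 0.7 they are 95% and 98%.

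**The significance rule taken literally.** In 15,000 simulated trials per scenario, screening baseline BDI-II by three-arm ANOVA put it in the model in about 5% of trials. Power for a post-test comparison was 81% under this rule and 94% with adjustment fixed in advance. The SD of the estimate was 1.19 against 1.00. Overall type I error under the rule was 4.1%.

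**Error given a near-miss imbalance.** In 200,000 simulated null trials (33 per arm, r = 0.6), baseline BDI-II differed between the two arms at 0.05<p<0.20 in 15.0%.

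| Use of baseline BDI-II | Type I error, all trials | Type I error given 0.05<p<0.20 at baseline |
|---|---|---|
| Not used | 5.0% | 10.1% |
| Change only | 5.1% | 8.3% |
| Covariate | 5.0% | 4.9% |

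Separate runs gave 9.7% to 10.3%, 7.9% and 4.6% to 4.8% for the last column, so about 10%, 8% and 5% is a fair summary.

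**The case against.** The strongest reply is that baseline BDI-II is very probably in the model. The abstract commits to adjustment for baseline scores. The Main analysis section describes a repeated-measures model with trajectories over the trial, and the Sample size section plans on four time points with a common baseline mean. The two texts can be read together: baseline scores are in, and other covariates are conditional. A reader might infer from the Main analysis section that baseline BDI-II will be left unadjusted. That follows only if the section is read alone, and the documents do not support it as a statement of the plan. It also means the 80% and 10% figures describe an analysis the article probably does not intend. The fairer comparison is then 88% against 94% for power, and 8% against 5% for conditional error.

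This reply narrows the point without removing it. The Main analysis section does not state the route by which baseline enters. A group-by-time contrast with freely estimated baseline means recovers only part of the gain.

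A reader might also infer that the trial's type I error is inflated. It is not: it stays at about 5% averaged over all trials, and the higher figures apply only to the roughly 15% with a near-miss imbalance. Nor does the rule let results be selected by outcome. The tests and the level are stated in advance and use baseline data only, and including a chance-imbalanced covariate does not in itself bias the treatment effect.

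**Conclusion.** The point holds in a limited form. The article states an explicit rule that selects primary-model covariates by baseline significance, so this is not a detail left to an unseen analysis plan. It also leaves unreconciled how baseline BDI-II is used. The consequence is inefficiency and conditional error under chance imbalance: 6 percentage points of power (88% to 94%) if baseline enters only through change, and 14 (80% to 94%) if it is not used at all. The stated sample size need not increase.

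The figures rest on the protocol's planning values, on normally distributed scores, and on a two-arm comparison at post-test rather than the full four-time mixed model. They concern the main comparison, face-to-face MBI versus TAU.

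**What to change.** 1. State in the Main analysis section, in line with the abstract, that baseline BDI-II is always included: either as a covariate, or as the first time point with a common mean across arms.
2. Delete the rule that adjusts for significantly different variables. Replace it with a short list of prognostic covariates, fixed before analysis and drawn from variables already collected at baseline, or with no further covariates.
3. Report baseline characteristics by arm descriptively, without tests that drive the model.

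The cost is a change of wording, with no extra patients or data. Because the secondary comparisons follow the same strategy, one change corrects them too. The article describes the trial as still recruiting, so the change could be made before analysis.

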### Secondary analysis

The efficacy of the “face-to-face MBI + TAU” group compared to the “TAU alone” group with regard to the secondary outcomes and the other measures, and the efficacy of the “Internet-delivered MBI + TAU” compared to the “TAU alone”, as well as the exploratory comparison of the “face-to-face MBI + TAU” and “Internet-delivered MBI + TAU” on the primary and secondary outcomes, will be calculated following the same analytical strategy used for the main analysis. Per protocol analysis will also be performed, considering only those patients who attend at least 3 modules (out of 4). The clinical significance of improvements between groups will be explored by calculating the absolute risk reduction and number needed to treat (NNT) (and their 95% CI). We will use two criteria for improvement: a) changing to a less severe cluster in the BDI-II compared to the one the patient was allocated to at baseline; c) calculating the clinical significance of improvements by establishing both the cut-off point and reliable change index on the BDI-II total score using the Jacobson and Truax method [66]. Additionally, possible differences in PHQ-9 and PANAS will be explored throughout the MBI modules using mixed models.

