### Interventions

#### Mindfulness-based interventions (MBIs)

The two MBIs (face-to-face and Internet delivered) are composed of an initial face-to-face group (6-8 participants) session to introduce the therapeutic modules, explain how mindfulness can help patients with their problem, and motivate them to change. In the case of online patients, the therapist will also explain how to enter the web page where the therapeutic modules are located. Thus, both conditions are composed of four modules, face-to-face or online, depending on the assigned condition. Regardless of the condition, all the patients will receive their corresponding TAU.

- “*Face-to-face MBI” sessions* will be carried out in a group format (between 6 and 8 participants) and with weekly sessions lasting 90 min each for 4 weeks. The therapist will explain the different modules and how to do the mindfulness exercises. The mindfulness activities will be performed in the sessions, and then participants will have to practice at home. All the materials will be delivered in print form, except the audios, which will be sent by e-mail. However, the audios will also be transcribed in the printed modules. Module contents are the same as those in the online intervention. These contents have been adapted from an online format previously used [10] to a traditional format for their application in this study. If a participant does not attend a session, the corresponding materials will be delivered to him/her, and s/he will be able to ask any questions about them in the next session.

- “*Internet-based MBI”* will be carried out online and individually through a web platform (https://www.psicologiaytecnologia.com/) where participants will have to introduce a login and a password to enter their corresponding profiles. The duration of each module will be approximately 60-90 min, depending on the participant’s pace and time availability, and the estimated program duration for most people will be between 4 and 8 weeks [10]. Some meta-analyses have shown that attrition rates are higher when no therapist support is provided to patients in Internet-based programs [21, 42]. For this reason, when the patients complete the second module (halfway through the program), they will receive a phone call from the therapist who will monitor their progress and motivate them to continue and adhere to the program. However, no additional therapeutic content will be offered.

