#### Treatment as usual (TAU)

Participants in the treatment as usual (TAU) arm will continue to be treated by their GPs in their corresponding health centers. The treatments offered by the GPs are mainly pharmacological, with antidepressants and/or anxiolytics being the most frequent medications. In cases of suicide risk or other severe symptoms or unexpected effects during the study, the patient will be referred to specialized mental health care services and excluded from the data analysis.

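### The per-protocol rule of at least 3 of 4 modules has no counterpart in TAU, so the secondary per-protocol contrast with TAU is not protected by randomisation

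*Protocol article*

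**What the plan says.** The rule stands in the Protocol article, Secondary analysis: "Per protocol analysis will also be performed, considering only those patients who attend at least 3 modules (out of 4". It follows a list of comparisons that includes face-to-face MBI versus TAU on the secondary outcomes, "the efficacy of the “Internet-delivered MBI + TAU” compared to the “TAU alone", and an exploratory comparison of the two formats.

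Modules belong to the two programmes only. Under Mindfulness-based interventions (MBIs), "both conditions are composed of four modules, face-to-face or online, depending on the assigned condition". The section on TAU describes ordinary care: "Participants in the treatment as usual (TAU) arm will continue to be treated by their GPs in their corresponding health centers". Per the Ethics section, TAU patients are offered the programme only once the study is over. No per-protocol criterion for TAU is given anywhere.

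The Main analysis section puts the primary comparison on an intention-to-treat basis. The abstract gives the per-protocol work secondary status: "Per-protocol secondary outcome analyses will also be performed". For the MBI groups, the section on treatment expectations, opinions and completion adds: "In addition, a module completion register will be filled out".

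**The concern.** A rule about modules cannot sort patients who have none. There are two ways to apply it:

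- **Literally.** No TAU patient qualifies, and no per-protocol contrast with TAU remains.
- **As probably intended.** TAU stays whole and only the MBI arms are filtered on what patients did after randomisation. MBI patients who attend fewer than three modules are removed, while their counterparts in TAU, who cannot be identified, stay in.

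Under the second reading the groups are no longer comparable by design. If people who complete modules would have had a different BDI-II course anyway, that difference enters the estimate as if it were treatment effect. A per-protocol result larger than the intention-to-treat result could then be read as the effect of taking the programme properly, when part of it is selection.

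**Working it through.** **1. Plan's own figures.** The Sample size section uses d = 0.7, SD 5 and a 3.5-point difference: 0.7 × 5 = 3.5. A two-sided 5% test with 80% power gives 2 × (1.960 + 0.842)² × 5² / 3.5² = 32.04, rounded up to 33 per group, as stated. The document gives no figure for the per-protocol analysis.

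**2. Bias formula.** Let *a* be the share of MBI patients who attend at least 3 modules, and δ the gap, in SD units, between would-be non-adherers and would-be adherers in BDI-II without the programme. Suppose the programme has no effect. The retained MBI mean is then the adherers' mean. The TAU mean is *a* × adherers' mean + (1 − *a*) × non-adherers' mean. The spurious MBI advantage is

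(1 − *a*) × δ × SD.

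**3. Numbers.** SD = 5 is from the plan. The document gives neither *a* nor δ; the ranges below are assumptions.

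| *a* | δ | Bias (points) | Share of 3.5 |
|---|---|---|---|
| 0.8 | 0.2 | 0.2 × 0.2 × 5 = 0.2 | 6% |
| 0.8 | 0.6 | 0.2 × 0.6 × 5 = 0.6 | 17% |
| 0.6 | 0.2 | 0.4 × 0.2 × 5 = 0.4 | 11% |
| 0.6 | 0.6 | 0.4 × 0.6 × 5 = 1.2 | 34% |

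With δ = 0 the bias is zero. With δ negative (adherers have the worse prognosis) the sign reverses.

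**4. Cross-check with a second model.** Let attendance follow a latent normal variable correlated *r* with better outcome. The bias is *r* × 5 × φ(c)/p, with p the share attending at least 3 modules, c the normal quantile of 1 − p, and φ the normal density. For *r* = 0.1 to 0.5 (assumed), this is 0.17 to 0.87 points at p = 0.8 and 0.32 to 1.61 points at p = 0.6. The top of this range exceeds 1.2 because *r* = 0.5 at p = 0.6 implies a gap of about 0.8 SD (1.61 / (0.4 × 5)), wider than in step 3. In 20,000 simulated null trials per scenario (unadjusted t-test, 40 TAU patients against the attenders among 40 MBI patients), the two-sided 5% test rejected in 5% to 11% of trials at p = 0.8 and in 6% to 23% at p = 0.6.

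**5. Effect of baseline adjustment.** The abstract describes models adjusted for baseline scores. As an illustration, express the gap in residual SD with the plan's correlation of 0.6: 5 × √(1 − 0.6²) = 4.0. The range falls to 0.2 × 0.2 × 4 = 0.16 up to 0.4 × 0.6 × 4 = 0.96 points, or 5% to 27% of 3.5.

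**6. Does an instrumental-variable estimate avoid the problem?** The simple complier estimate is the intention-to-treat difference divided by the share exposed. It removes nobody. With a 3-module threshold, however, patients with one or two modules count as unexposed. If a share *b* has such partial exposure with effect E₁, and full exposure has effect E₂, the estimate is (*a*E₂ + *b*E₁)/*a* = E₂ + (*b*/*a*)E₁. It is inflated whenever partial exposure helps, so the threshold has to be reconsidered together with the method.

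**The case against.** The case for leaving the plan alone is that this is a secondary analysis, no efficacy conclusion is tied to it, and any per-protocol comparison of a programme with usual care loses the protection of randomisation. How controls enter the set could also be settled in an analysis plan that is not shown. The first part stands and limits the consequence. The second helps less: the printed rule is a stated criterion that does not work for TAU, and even if TAU is retained in full the selection in the MBI arms remains.

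It is also fair that the size is assumed and that baseline adjustment may reduce it (step 5).

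Three stronger readings are tempting, and the document does not support them:

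- **That the analysis will overstate the MBI effect.** A reader might infer this because adherers often do better. The document says nothing about who attends, so the direction is an assumption.
- **That the two MBI arms are counted by different rules.** A reader might infer this from the provision for missed face-to-face sessions: "If a participant does not attend a session, the corresponding materials will be delivered to him/her". That sentence does not say how such a module counts. The per-protocol rule speaks of modules, and a completion register is planned for the MBI groups. Different counting is not established.
- **That the trial's main conclusion is at risk.** This rule does not enter the intention-to-treat analysis.

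**Conclusion.** The point holds for the secondary per-protocol contrasts of either MBI arm with TAU. The rule as printed either empties the TAU arm or selects on post-randomisation attendance in the MBI arms only. That follows from the text and needs no assumption.

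The bias does rest on assumptions. At 60-80% adherence, a gap of 0.2-0.6 SD and SD 5, it is about 0.2-1.2 BDI-II points (6-34% of 3.5). These figures apply where the per-protocol analysis is run on BDI-II. The contrast between the two MBI formats is outside this point: the rule can be applied in both arms there, although both sides are then selected after randomisation.

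**What to change.** 1. For each MBI arm versus TAU, make the adherence analysis a complier-average estimate with randomised arm as the instrument and all randomised patients kept. Non-adherence is one-sided, because TAU patients are offered the programme only at the end of the study.
2. Take exposure from the module completion register in both MBI arms. Define it as any module completed or as the number completed, or report the 3-module version only as a sensitivity analysis (step 6). The separate review question concerns the last module seen in session and cannot replace the register.
3. State the exclusion restriction: assignment acts on BDI-II only through the exposure as defined. Discuss it in light of the introductory session and the materials delivered after a missed session.
4. If the 3-of-4 subset is still shown, say that all TAU patients are retained, label it descriptive and draw no efficacy conclusion from it.
5. Reconcile keeping all randomised patients with the post-randomisation exclusions from analysis in the eligibility section (medication increase, other psychological treatment) and in the TAU section (referral to specialised care).

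The cost is revised wording and a little programming, with no new data. The price is precision and an untestable assumption. If the standard error scales as 1/share exposed, the confidence interval is about 1/0.8 = 1.25 to 1/0.6 = 1.67 times as wide as the intention-to-treat interval at 80% and 60% exposure.
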